### Randomization and Blinding

The randomization sequence will be generated by the data manager. The patients will be randomly assigned to either the treatment group or the control group in a 1:1 ratio. Blinding methods will not be used in this clinical trial. Although blinding of participants is not feasible due to the nature of the intervention, the following blinding strategies will be implemented in the study design to minimize potential bias: health care providers administering the treatment, outcome assessors, and data analysts will all be kept blinded to group allocation. Specifically, the treatment providers responsible for assigning the interventions will not participate in subsequent efficacy or safety evaluations. During follow-up visits, clinical assessors will perform dermatological lesion observation and grading without knowledge of the participants’ group assignments. For the final statistical analysis, analysts will process data using anonymized codes, and blinding will only be lifted after the statistical analysis is completed. This approach was designed to ensure objectivity and accuracy in outcome evaluation and data interpretation.

### Interventions

In the treatment group, after EGFR-TKI treatment, patients will receive daily oral TCM-based granule treatment. The prescription consists of *A membranaceus* (30 g), *I indigotica Fort* (15 g), and *C margaritifera* (15 g). The granules will be taken twice daily, in the morning and evening, following meals for 7 days per treatment course, with 2 consecutive courses administered. In the control group, patients will apply the urea ointment to the affected areas daily, 1 to 3 times per day, with each course lasting 7 days, also for 2 consecutive courses. All medications were supplied by Shanxi Provincial Hospital of Traditional Chinese Medicine. Investigators will assess patients on days 0, 3, 7, and 14 (Table 1). During the observation period, all patients will avoid contact with irritants, particularly in areas prone to rash, and will use sunscreen daily to reduce the incidence of skin rashes.

**Table 1. T1:** Schedule of the jiedu xiaozhen granule clinical trial.

	Visit 0 (day 0; ±2 days)	Visit 1 (day 3; ±2 days)	Visit 2 (day 7; ±2 days)	Visit 3 (day 14; ±2 days)	Visit 4 (3, 6, 9, 12, 15, 18, 21, and 24 months)
Signature of the informed consent form	✓				
Inclusion and exclusion criteria for verification	✓				
Randomization grouping	✓				
Release of experimental drugs	✓				
Recovery of the experimental drugs				✓	
Basic data collection					
Demographic data	✓				
Personal history and allergy history	✓				
Study disease–related history	✓				
Evaluation of the condition and its effectiveness^a^	✓	✓	✓	✓	
History of other diseases	✓				
Concomitant medications or treatment	✓	✓	✓	✓	
Security observations					
Liver and kidney function examination	✓			✓	
Untoward effect		✓	✓	✓	
Efficacy observation					
Clinical efficacy rate (NCI-CTCAE^b^ version 5.0)	✓	✓	✓	✓	
WoMo score	✓	✓	✓	✓	
Peak pruritus NRS^c^	✓	✓	✓	✓	
DLQI^d^	✓	✓	✓	✓	
EORTC QLQ-C30^e^ scale (quality of life measurement)	✓	✓	✓	✓	
Median PFS^f^					✓
Laboratory examination (FGF7^g^ and HGF^h^ in human blood)	✓	✓		✓	
Skin histopathological examination	✓				
Evaluation of medication compliance		✓	✓	✓	
Adverse events and complications		✓	✓	✓	
Serious adverse events		✓	✓	✓	

a A systematic and comprehensive evaluation of patients with non–small cell lung cancer was conducted in accordance with the Response Evaluation Criteria in Solid Tumors (RECIST 1.1), encompassing changes in pulmonary lesions and metastatic foci, as well as indicators such as tumor marker.

b NCI-CTCAE: National Cancer Institute Common Terminology Criteria for Adverse Events.

c NRS: numerical rating scale.

d DLQI: Dermatology Life Quality Index.

e EORTC QLQ-C30: European Organisation for Research and Treatment of Cancer Quality of Life Questionnaire Core 30.

f PFS: progression-free survival.

g FGF7: fibroblast growth factor 7.

h HGF: hepatocyte growth factor.

To uphold the integrity of the study, participants are permitted to engage in fundamental skin care regimens throughout the trial and will maintain diligent sun protection measures and refrain from indulging in excessive cleansing or the application of abrasive cosmetics on a daily basis. Nevertheless, it is imperative to abstain from the ingestion of any other pharmacological agents or the implementation of interventions that could potentially disrupt the therapeutic process for the rash, encompassing, though not restricted to, hormonal medications and immunosuppressants. Should any significant cutaneous discomfort or additional complications arise, it is essential to promptly notify the attending physician for a timely evaluation and modification of the treatment plan if necessary.

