**Results:**

The clinical trial registration was completed in October 2024. This study is currently underway. As of December 1, 2025, a total of 81 eligible participants had been enrolled, all of whom were assigned to groups following the randomization principle. Among them, 42 participants were allocated to the JDXZ group (with an additional 2 participants pending enrollment), and 39 to the control group. Based on the current progress, the estimated trial completion date has been extended to January 31, 2026.

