## Methods

### Study Design

This study is a multicenter, prospective, randomized controlled clinical trial in which participants will receive either enhanced TCM or positive control drugs. The trial will involve 94 patients with a confirmed diagnosis of *EGFR* gene mutation–positive NSCLC who developed skin rashes after using EGFR-TKIs. The participants will be divided into 2 groups: the treatment group (receiving oral JDXZ granules) and the control group (receiving topical urea ointment). Effectiveness will be assessed by comparing baseline conditions with the results at 2 weeks after treatment. Each patient will undergo 4 scheduled visits: at baseline and on days 3, 7, and 14 (Figure 1).

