##### Withdrawal Criteria

Patients will be withdrawn from the study if they experience serious adverse events, such as nausea, vomiting from oral TCM, or liver and kidney insufficiency, making further observation unsuitable. Additionally, patients who fail to complete the treatment and observation period outlined in the protocol for any reason will be considered for withdrawal. Patients unwilling to continue treatment and requesting to exit the trial will also be withdrawn. Finally, any disease progression that affects or interferes with the study outcomes will result in the withdrawal of the patient from the trial.

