#### Secondary Outcomes

The secondary outcomes include the WoMo (Wollenberg and Moosmann) score, which ranges from 0 to 100 and is calculated using the formula final score= 1/4A + 1/4B + 10/3C. Acnelike rash scores of 0 to 20 are considered mild, scores of 21 to 40 are considered moderate, and scores of 41 to 100 are considered severe (Multimedia Appendix 1). Other outcomes include the peak pruritus numerical rating scale, which measures the intensity of pruritus; the dermatology Life Quality Index, which assesses the impact of skin disease on quality of life; the European Organisation for Research and Treatment of Cancer Quality of Life Questionnaire Core 30 scale (quality of life measurement), which evaluates overall quality of life in patients with cancer; median progression-free survival, which represents the time during which patients remain free from disease progression (follow-up every 3 months); a laboratory examination to measure changes in blood levels of factors such as fibroblast growth factor 7 and hepatocyte growth factor, and a skin histopathological examination to evaluate skin tissue changes after the treatment.

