## Results

This study is currently underway. As of December 1, 2025, a total of 81 eligible participants had been enrolled, all of whom were assigned to groups following the randomization principle. Among them, 42 participants were allocated to the JDXZ group (with an additional 2 participants pending enrollment), and 39 to the control group. Based on the current progress, the estimated trial completion date has been extended to January 31, 2026.

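### The 24-month progression-free survival schedule cannot be completed by the only stated completion date, 31 January 2026, and the withdrawal rule does not say that progression still counts as an event

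*Protocol article*

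**What the plan says.** The Secondary Outcomes section lists "median progression-free survival, which represents the time during which patients remain free from disease progression (follow-up every 3 months"). Table 1, in the Interventions section, sets the time points as "Visit 4 (3, 6, 9, 12, 15, 18, 21, and 24 months"). PFS is the only item ticked in that column. The Study Design section describes a shorter trial: "Each patient will undergo 4 scheduled visits: at baseline and on days 3, 7, and 14".

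On dates, the Abstract says "The clinical trial registration was completed in October 2024". The Results section says "As of December 1, 2025, a total of 81 eligible participants had been enrolled", and then "Based on the current progress, the estimated trial completion date has been extended to January 31, 2026". It gives no other completion date and no date of first enrolment. The target is 94 patients.

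The Withdrawal Criteria section ends with the rule that "any disease progression that affects or interferes with the study outcomes will result in the withdrawal of the patient from the trial". It does not say whether PFS status is still collected or counted after such a withdrawal.

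**The concern.** PFS is the only outcome followed beyond day 14. The protocol does not state why it is collected. However, the Introduction says that rash severity tends to go with treatment response, and the Discussion says that rash predicts EGFR-TKI benefit, so readers will look at PFS in a trial that treats the rash.

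Two things in the text work against it. First, a schedule that runs to month 24 is paired with a completion date about 16 months after registration and about 2 months after the latest enrolment count. If data collection stops on that date, most patients are followed for only part of the schedule and some have no PFS visit at all.

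Second, a patient withdrawn at progression may be handled as a dropout. If such patients are censored at withdrawal, events are lost and PFS looks longer than it is.

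**Working it through.** **Inputs.** From the Abstract and Results: registration October 2024; 81 enrolled on 1 December 2025 (42 + 39); estimated completion 31 January 2026. From Study Design and Sample Size: target 94. From Table 1: PFS visits every 3 months to month 24. The plan gives no calculated figure for PFS, so there is none to reproduce. The sample size of 78, raised to 94, concerns the rash response rate only. One month is taken as 30.4375 days.

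**Step 1: latest enrolment date for each visit.** Latest date = 31 January 2026 minus the visit month.
- Month 24: 31 January 2024.
- Month 18: 31 July 2024.
- Month 3: 31 October 2025.

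The first two fall before registration.

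**Step 2: longest possible follow-up.** This is the completion date minus the first enrolment date, which has to be assumed.

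| Assumed first enrolment | Longest follow-up (months) |
|---|---|
| 1 July 2024 (before registration) | 19.0 |
| 1 October 2024 | 487 / 30.4375 = 16.0 |
| 31 October 2024 | 457 / 30.4375 = 15.0 |
| 1 January 2025 | 13.0 |

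With no enrolment before October 2024, nobody reaches month 18, 21 or 24. Even a start on 1 July 2024 would leave months 21 and 24 empty.

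**Step 3: the last patients.** 94 − 81 = 13 remain to be enrolled after 1 December 2025. From that date to 31 January 2026 is 61 / 30.4375 = 2.0 months, so all 13 miss the 3-month visit.

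**Step 4: illustrative counts.** These assume even accrual of the 81 from October 2024, and 0.5 to 2.0 months of follow-up for the other 13.

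| Follow-up at least (months) | Start 1 Oct 2024 | Start 31 Oct 2024 |
|---|---|---|
| 3 | 75 of 94 | 74 of 94 |
| 6 | 58 | 56 |
| 9 | 41 | 37 |
| 12 | 23 | 19 |
| 15 | 6 | 1 |
| 18 | 0 | 0 |

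Mean follow-up is 7.5 to 7.9 months.

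**Step 5: would a median still be reached?** The documents give no PFS rate, so a range of true medians is assumed. The check simulated exponential PFS with the same median in both arms, 47 per arm, the follow-up pattern of Step 4, exact event times and no dropout (1,000 runs per row). Ranges cover the two October start dates.

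| Assumed true median (months) | Expected events | Probability that both arms' Kaplan-Meier medians are reached |
|---|---|---|
| 6 | 49–51 | 0.99–1.00 |
| 9 | 38–40 | 0.83–0.84 |
| 12 | 31–32 | 0.42–0.50 |
| 18 | 23–24 | 0.08–0.11 |
| 24 | 18–19 | 0.01–0.02 |

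**Step 6: when the schedule would really end.** A patient randomised on 1 December 2025 reaches month 24 on 1 December 2027. If the last day-14 visit is to fall by 31 January 2026, the last randomisation is about 17 January 2026, and month 24 falls in January 2028.

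**Step 7: progression and withdrawal.** Secondary Outcomes makes freedom from progression the quantity measured. Withdrawal Criteria removes patients whose progression affects the study outcomes. Since PFS is one of those outcomes, progression can be read as meeting the condition. Nothing in either section says which reading applies or that the event is kept.

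**The case against.** The strongest reply is that the January 2026 date is only an estimate, already moved once, and may refer to the 14-day treatment phase. That is possible, but no section says so: the document calls it the trial completion date and ties publication to completion of the trial. If only the short phase is meant, PFS has no completion date, and the text still needs correcting.

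Several stronger readings are tempting, but the documents do not support them.
- **A reader might infer that a median PFS cannot be obtained.** Step 5 shows that this depends on the true PFS. A truncated Kaplan-Meier median is very likely to be reached if PFS is around 6 months and unlikely at 18 months or more.
- **A reader might infer that PFS will be analysed with a t test or rank test.** The Statistical Analysis section names no method for censored times, but it assigns none of its tests to PFS and states no between-group PFS test. Survival methods may sit in the analysis plan or full protocol, which are not shown. Their absence here is context only.
- **A reader might infer that every progression leads to withdrawal and is lost.** The rule is conditional, and it does not say that progression goes unrecorded. What stands is that the conflict is left open.
- **A reader might see a flat contradiction in the four visits of Study Design.** That sentence describes the two-week phase and points to Figure 1, whose legend mentions 3-monthly PFS follow-up. The wording needs aligning but is weak evidence by itself.

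It is also fair to say that PFS is one of several secondary outcomes in a trial labelled exploratory.

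**Conclusion.** The point holds in limited form. The PFS schedule and the stated completion date are incompatible: by 31 January 2026 follow-up is at most 15 to 16 months, no patient reaches months 18, 21 or 24, and the 13 patients enrolled after 1 December 2025 miss even month 3. This rests on one assumption, that enrolment did not begin before October 2024. A later start shortens follow-up further. The Step 4 counts also assume even accrual and are illustrative.

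Separately, the withdrawal rule leaves it unclear whether progression is kept as a PFS event.

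The scheduled 24-month follow-up is what cannot be delivered by that date; the documents do not settle whether a median would be reached. The primary outcome at day 14 and its sample size are untouched, so this should be corrected but is not a must-fix.

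**What to change.** Reconcile Study Design, Withdrawal Criteria, Table 1, Secondary Outcomes and Results in one of two ways.
1. **Keep the schedule.** Give PFS its own completion date, 24 months after the last randomisation (about December 2027 to January 2028), and report it separately from the day-14 analysis. Randomization and Blinding lifts the blind once the statistical analysis is completed, so it should then say which analysis is meant.
2. **Keep the date.** State that PFS is exploratory and administratively censored at a named data cut, and delete the visits that nobody can reach.

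In both cases, state the date of first enrolment, count progression or death as a PFS event and not as a withdrawal, say that PFS status is collected after a patient leaves the study for progression, and report a median only if it is reached. This concerns how the outcome is counted, not clinical management after progression.

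The cost is wording, plus either a later PFS report with follow-up to about January 2028 or a more limited PFS claim with no added follow-up.

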### Assessments

#### Primary Outcomes

In conformity with the NCI-CTCAE version 5.0 and the efficacy assessment criteria in alignment with the *Guiding Principles for Clinical Research on New Chinese Medicine Drugs* [32], the criterion for improvement was defined as a posttreatment rash grade of 0, denoting complete recovery. A ≥2-grade improvement in the rash classification was defined as a marked effect. A single-grade improvement in the rash classification was deemed effective. Should these criteria not be satisfied and the rash either remain unaltered in severity or worsen by more than 1 grade, the treatment will be regarded as ineffective. The following formula will be used: clinical efficacy rate=(cured + significantly improved + improved cases)/total cases × 100% .

#### Secondary Outcomes

The secondary outcomes include the WoMo (Wollenberg and Moosmann) score, which ranges from 0 to 100 and is calculated using the formula final score= 1/4A + 1/4B + 10/3C. Acnelike rash scores of 0 to 20 are considered mild, scores of 21 to 40 are considered moderate, and scores of 41 to 100 are considered severe (Multimedia Appendix 1). Other outcomes include the peak pruritus numerical rating scale, which measures the intensity of pruritus; the dermatology Life Quality Index, which assesses the impact of skin disease on quality of life; the European Organisation for Research and Treatment of Cancer Quality of Life Questionnaire Core 30 scale (quality of life measurement), which evaluates overall quality of life in patients with cancer; median progression-free survival, which represents the time during which patients remain free from disease progression (follow-up every 3 months); a laboratory examination to measure changes in blood levels of factors such as fibroblast growth factor 7 and hepatocyte growth factor, and a skin histopathological examination to evaluate skin tissue changes after the treatment.

#### Adverse Events

In conformity with the criteria delineated by the Ministry of Health of China’s Adverse Drug Reaction Monitoring Center, as documented in the *Guiding Principles for Clinical Research of New Chinese Medicine Drugs*, the potential relationship between adverse events and the use of the investigational drug will be appraised using a 5-tiered categorization scheme encompassing “certain,” “probable,” “possible,” “remote,” and “unrelated.” The specific evaluation metrics are meticulously outlined in the adverse event table, which is an integral component of the study’s records (Multimedia Appendix 2).

Researchers must prompt patients to honestly report medication effects, steer clear of suggestive questions, and document any adverse reactions on the adverse event form. Follow-up, including detailed records and laboratory test normalization, should continue until symptoms resolve via hospital visits, outpatient checks, or other methods based on reaction severity (Multimedia Appendix 2).

Upon detecting adverse reactions, the researchers will diagnose, treat, and decide whether to halt observation based on the condition. For serious events, the study unit must act promptly to ensure participant safety. Researchers will submit the serious adverse event report form to the oncology department, the ethics committee, and all participating units of the hospital within 24 hours, signing and dating it.

### Data Collection and Management

Informed consent will be enhanced by detailing the study’s purpose, procedure, potential discomfort, and risks, ensuring voluntary participation. Effective physician-patient communication will be fostered, promptly addressing patient needs and resolving treatment issues to boost compliance. A follow-up plan will be developed to minimize participant burden, and phones and SMS text messages, among other tools, will be used to increase follow-up rates.

Data will be collected and recorded in a case report form by trained researchers. Baseline assessment data will be collected on the sociodemographics of the patients (including gender, age, educational level, religion, marital status, occupation, income, economic burden of illness, caregiver during illness, and smoking and drinking history), as well as disease duration and any previous treatment with TCM. Medical records of clinical trial participants, both inpatient and outpatient, should be stored at the hospital to create an electronic case database.

Researchers must document medical records concurrently with treatment to ensure timeliness, completeness, and accuracy. Any corrections should be underlined and dated by the researchers without altering the original entry. The CRF Questionnaire and Adverse Event Recording Survey, completed by both the patient and physician, adheres to objectivity and sincerity. Objectivity pertains to neutral instrument design and data authenticity, mitigating researcher bias. Respondent sincerity reflects truthful participation, minimizing social desirability bias. Their synergy ensures data reliability and study validity. Value ranges and logic will be regularly verified. For uncertainties, the question list will be completed, and researchers will address the listed queries. Main concerns include the standardization of the components of Chinese herbal preparations and their quality; potential interference from concomitant medications; and possible subjectivity in skin toxicity assessment indicators. Upon finishing the data verification report, the database will be secured. Quality control documents will be kept, including records of data consistency checks, value range and logic verifications, blind audits, and researcher communications.

### Statistical Analysis

Data will be analyzed using SPSS Statistics for Windows (version 26.0; IBM Corp). Continuous data following a normal distribution will be expressed as means and SDs and compared within groups using a paired 2-tailed *t* test or between groups using an independent-sample 2-tailed *t* test. Data will be presented as frequencies and percentages, with chi-square tests for group comparisons and rank sum tests for ranked data. For continuous data that are not normally distributed, between-group comparisons will be performed using the Mann-Whitney *U* test, with data described as medians and IQRs. For measurements involving multiple time points, nonparametric methods such as the Friedman test will be used to ensure robust and reliable findings. A *P* value of <.05 will be considered statistically significant.

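### The between-arm tests named for the continuous secondary outcomes have no baseline covariate although day-0 values are collected; they are valid on average but less precise than a baseline-adjusted comparison

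*Protocol article*

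**What the plan says.** The Statistical Analysis section gives two between-arm methods for continuous data. Normally distributed data are compared "between groups using an independent-sample 2-tailed" *t* test. For the rest, "between-group comparisons will be performed using the Mann-Whitney" *U* test.

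Two other tests in that paragraph use repeated values, but neither compares the arms. The paired *t* test is stated to be within groups. The Friedman test is within subject: "For measurements involving multiple time points, nonparametric methods such as the Friedman test will be used". No analysis of covariance, mixed model or other baseline adjustment is named.

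Baseline data will exist. The Interventions section states "Investigators will assess patients on days 0, 3, 7, and 14", and Table 1 ticks WoMo, peak pruritus NRS, DLQI, QLQ-C30 and the FGF7/HGF blood test at Visit 0 and again at day 14.

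The quantity to be tested is only partly fixed. Study Design says "Effectiveness will be assessed by comparing baseline conditions with the results at 2 weeks after treatment", without saying how baseline enters the comparison between arms. Secondary Outcomes describes the biomarkers as "a laboratory examination to measure changes in blood levels of factors such as fibroblast growth factor 7 and hepatocyte growth factor", so change is the natural quantity for FGF7 and HGF. The four scales are listed simply as scores.

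**The concern.** Eligibility admits rash grades 1 to 3, so WoMo, itch and DLQI will differ between patients at entry and can reasonably be expected to predict day 14 to some degree. A two-sample test on day-14 values leaves that explained variation in the error term. A two-sample test on changes subtracts the whole baseline value, which over-corrects when the correlation is modest. In both cases a chance difference between arms at day 0 carries partly into the estimate: in the same direction for day-14 values, in the opposite direction for changes.

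At stake are the precision of the JDXZ-versus-urea estimates for six secondary outcomes in a small trial, and how they read if the arms happen to differ at baseline. The primary clinical efficacy rate already uses the baseline grade by its definition, and progression-free survival is a time-to-event outcome. Neither is part of this point.

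**Working it through.** **Plan's own figure.** There is none to reproduce. The Sample Size section concerns a binary response rate and gives no power or precision for the continuous secondary outcomes.

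**Inputs.**
- n = 39 per arm: 78 evaluable in total (Sample Size), allocated 1:1 (Randomization and Blinding).
- Two-sided 5% level (Statistical Analysis).
- Assumed, not in the article: correlation ρ between the day-0 and day-14 values of 0.3 to 0.7, equal SDs at both times, and an illustrative true difference of 0.5 SD.

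**Step 1: standard error.** In SD units, the standard error of the arm difference is √(2/n × f), where f is 1 for day-14 values, 2(1−ρ) for changes and 1−ρ² for baseline adjustment. For day-14 values this is √(2/39) = 0.226. Power is from the noncentral *t* distribution with noncentrality 0.5 / SE.

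| ρ | SE, change | SE, adjusted | Power, day-14 | Power, change | Power, adjusted | Variance cut, adjusted vs day-14 |
|---|---|---|---|---|---|---|
| 0.3 | 0.268 | 0.216 | 59% | 45% | 63% | 9% |
| 0.5 | 0.226 | 0.196 | 59% | 59% | 71% | 25% |
| 0.6 | 0.203 | 0.181 | 59% | 68% | 78% | 36% |
| 0.7 | 0.175 | 0.162 | 59% | 80% | 86% | 49% |

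The ratio of the change factor to the adjusted factor is 2(1−ρ)/(1−ρ²) = 2/(1+ρ), which exceeds 1 for every ρ below 1. The factor 1−ρ² treats the slope as known. Estimating it multiplies the variance by about 1 + 1/(2n−4) = 1 + 1/74 = 1.014, so 0.91 at ρ = 0.3 becomes 0.92. The ordering does not change.

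**Step 2: size of chance imbalance.** The SD of the difference in baseline means is √(2/39) = 0.226 SD, and its 95% range is ±1.96 × 0.226 = ±0.44 SD. A difference above 0.3 SD in either direction has probability 18.5% at 39 per arm and 14.6% at 47.

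**Step 3: effect of an imbalance.** An imbalance d shifts the day-14 difference by ρd and the change difference by −(1−ρ)d. For d = 0.44 SD:
- ρ = 0.3: day-14 shift 0.3 × 0.444 = 0.13 SD; change shift −0.7 × 0.444 = −0.31 SD.
- ρ = 0.6: day-14 shift 0.6 × 0.444 = 0.27 SD; change shift −0.4 × 0.444 = −0.18 SD.

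**Step 4: type I error of the day-14 test.** Given an imbalance of 1.96 standard errors, the test statistic is centred at 1.96ρ with SD √(1−ρ²), against a critical value of 1.99 (76 degrees of freedom).
- ρ = 0.6: (1.99 − 1.18)/0.80 = 1.02, which gives 15.4%.
- ρ = 0.3: (1.99 − 0.59)/0.954 = 1.47 gives 7.1%; the other tail adds 0.3%, for 7.4%.

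Averaged over all randomisations the rate is 5%. In a simulation of 10,000 trials at each of ρ = 0.3, 0.5 and 0.7, it was 5.1%, 5.2% and 5.2% overall, and 6.7%, 11.2% and 18.0% among trials with a baseline imbalance above 0.3 SD.

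**The case against.** A reader might infer that the plan ignores baseline altogether. The article does not support that. FGF7 and HGF are described as changes, so day 0 enters by subtraction, and the Study Design sentence is compatible with change scores for the four scales too. A *t* or Mann-Whitney test can be run on changes. This part of the objection stands. It limits the point to the absence of a covariate, because a change score is still less precise than adjustment at every assumed ρ and still responds to imbalance.

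A reader might also infer that the named tests are biased or run at a 15% error rate. They do not. Randomisation keeps the overall rate at 5%. The 15% needs an imbalance at the edge of its 95% range, which about 1 trial in 20 reaches or exceeds, together with ρ = 0.6. At ρ = 0.3 the same imbalance gives about 7%.

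The size of the gain also rests on inputs the article does not supply. At ρ = 0.3, adjustment raises power over the day-14 test only from 59% to 63%. If changes are tested and ρ is 0.7, the step is from 80% to 86%. The trial is declared exploratory, and only secondary outcomes are affected. All of this stands and keeps the point modest.

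Finally, an article condenses, and covariate adjustment is often left to an analysis plan. That does not remove the point, because the article positively names unadjusted two-sample tests. If a fuller plan adjusts for baseline, the two texts need to be reconciled.

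**Conclusion.** The point holds as one of efficiency and robustness, not of validity. For WoMo, pruritus NRS, DLQI, QLQ-C30, FGF7 and HGF, the between-arm tests named make less use of the day-0 value than the data allow, whichever quantity is tested. Under the assumptions above, adjustment removes 9% to 49% of the variance of a day-14 comparison, and its power advantage is 4 to 27 percentage points over day-14 values and 6 to 18 points over changes. The gain over the day-14 test is small at the low end of the assumed correlations and substantial at the high end. Conditional error rises only in trials with a marked chance imbalance. Nothing here shows systematic bias or an inflated overall error rate. The change is worth making because it needs no new data and improves on both possible readings of the plan.

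**What to change.** Amend the Statistical Analysis section so that the between-arm analysis of each of the six outcomes is an analysis of covariance of the day-14 value on arm and that outcome's own day-0 value.

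- Analyse FGF7 and HGF on the log scale.
- For the bounded scales, choose robust standard errors or a rank-based analysis of covariance now, not after inspecting residuals.
- Report the adjusted JDXZ-minus-urea difference with its 95% CI.
- Keep the *t* and Mann-Whitney tests as sensitivity analyses, and state whether they use day-14 values or changes.

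**Cost.** No new patients, visits or measurements are needed. Trial Monitoring requires prior ethics committee approval for any protocol modification, so a short amendment is needed, and it should be in place before database lock and unblinded analysis. Time may be short: the Results section reports 81 enrolled by December 1, 2025, and estimates completion on January 31, 2026, and the article does not show whether the database has been locked. The method also adds a modelling assumption about the relation with baseline, which may be strained if many rashes clear and day-14 scores collect at zero. That is the reason to fix the robust or rank-based version in advance.
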